In Bangladesh, 100 sub-districts, across five of six divisions, were selected by BRAC as possible A&T intensive areas based on high poverty and stunting levels, and sub-districts that were not included in the government National Nutrition Program. This list was narrowed to 78 based on geographic proximity, size, and other operational aspects to ensure homogeneity across the sample. Within each division, four sub-districts were then randomly selected for inclusion in the evaluation sample using a computer program, for a total of 20 sub-districts. Sub-districts within each division were then randomly assigned, using a computer program, to either the *intensive* (10 sub-districts) or *non-intensive* (10 sub-districts) intervention. The randomization process was carried out in the presence of BRAC and A&T staff and the program evaluators in BRAC’s headquarters in Dhaka.

The baseline survey was conducted in 20 rural *upazilas* that are part of BRAC’s Essential Health Care (EHC) program platform for A&T. The baseline survey had three components—(i) household survey, (ii) community survey, and (iii) staff survey.

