## Sample size and power calculations

Sample sizes were estimated based on detectable differences between A&T and non-A&T *upazilas* for three separate sets of indicators: 1) exclusive breastfeeding (EBF) rates, 2) complementary feeding practices, and 3) stunting. Our sample size estimates accounted for randomization at the cluster (i.e., *upazila*) level rather than at the individual level. Surveys are repeated cross-sectional, surveying different households/children from the same communities.

The estimated sample sizes for each treatment arm, calculated prior to the baseline survey, was 500 infants 0-5.9 months old for EBF, 500 children 6-23.9 months old for complementary feeding-related practices, and 1,100 children 24-47.9 months old for stunting. Thus, the total proposed sample size was 4,200 children 0-47.9 months old. This sample size was estimated to allow us to detect expected differences in the outcomes outlined below, in a total of 20 clusters with an inter-cluster correlation (ICC) of 0.005, a significance level of 0.05, and power of 80 percent.

A sample size of 500 children aged 0-5.9 months of age was deemed sufficient to detect an increase in EBF rates by approximately 49 percent (from 43 percent to 64 percent); a sample size of 500 children aged 6-23.9 months of age is sufficient to detect an increase in several complementary feeding practices by at least 25 percent; a sample size of 1,100 children aged 24-47.9 months of age is sufficient to detect a reduction in stunting by 15 percent (from 43 percent to 36.5 percent).

Detailed sample size calculations are presented in **Table 3**.

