**Table 3: Sample size calculation for household survey**

|  | **Baseline sample size (same proposed for endline)** | **Baseline (%)** | **Detectable difference with sample size proposed for endline survey**** | **Intra-class correlation at baseline (estimated at upazila level)** | **Minimum sample size for detectable differences** |
| --- | --- | --- | --- | --- | --- |
| Stunting (24-47.9m) |  | 50.9 | 10 pp | 0.02 | 920 (detecting a 9 pp difference will require double this sample size) |
| HAZ (24-47.9m) |  | -2.0±1.2 | 0.35 | 0.05 | 519 |
| EBF (0-5.9m) |  | 49.9 | 20.0 | 0.12 | 390 |
| Minimum acceptable diet (6-23.9m) |  | 14.8 | 10 | 0.04 | 323 |
| Anemia among children  6-23.9 mo |  | 74.7 |  | 0.00 | 284 |

**Based on at least maintaining levels seen in the PE 2013 survey (where data available; data on stunting and anemia not available in PE 2013).*

***Detectable differences are estimated for endline-only comparisons between A&T-intensive and A&T-non intensive; double difference estimates will ensure greater statistical power.*

For the FLW survey at endline, we will again interview BRAC frontline workers delivering services in the 200 villages covered in the sampling for the evaluation. We estimate that the interviews would cover up to 300 SS, 100 SK, and 100 PK.

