## Detailed statistical analysis approach

The statistical analyses will include intent-to-treat analyses, unadjusted and adjusted, for primary impact indicators. Several other analyses related to establishing plausibility of impacts will also be undertaken.

1. **Impact estimates**

Impact estimates in Bangladesh will be double difference estimates of changes in key impact indicators. This takes into account changes over time between baseline and endline in the intervention and comparison groups, and differences between groups at these times. The impact estimates will yield (1) **percentage point and percentage changes** for IYCF practices and stunting, wasting, and underweight, and anemia (Bangladesh only); and (2) change in **mean Z scores** for height for age, weight for age, weight for height, and hemoglobin (Bangladesh only).

Analyses will be done separately for each critical age group, e.g., exclusive breastfeeding will be assessed only in children 0-5.9 months old, complementary feeding in children 6-23 months old and anthropometry impacts in children 24 months and above. These reflect the different sample age groups for the impact evaluation. All analyses are in Stata.

Analyses will focus on the following:

- ***Pure* *Intent-to-treat*** analyses based on the original evaluation design and original age groups, using child-level data and fixed-effects analysis to achieve double difference estimates. The fixed-effects analysis will account for village, the smallest level repeated between baseline and endline. Further adjustment for geographic clustering at provincial/divisional, district and commune/subdistrict level will be done using random- or fixed-effects to adjust for clustering if needed; the need for this is not likely because of the accounting of variation among villages.
- ***Pure intent to treat in high potential for exposure age groups* –** this analysis will focus on the stunting indicator and capture impact estimates in an age group of children who are mostly likely, because of their age, to have been exposed to A&T’s interventions early in infancy and for the longest duration. This is the 24-35 month age group in both Bangladesh and Vietnam. We will examine the pattern of HAZ across the full 0-59 month age range, and look at impacts on stunting beginning at the age when HAZ begins leveling off i.e. possibly beginning at 18 months of age. We will use fixed-effects regression models to adjust for village clustering as above.

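### Table 3's promise of extra power from double differencing is not guaranteed: with independent cross-sections the gain needs upazila means that correlate above 0.5 between rounds

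*Combined protocol and SAP*

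**What the plan says.** The second footnote to Table 3 gives the basis of the table: "Detectable differences are estimated for endline-only comparisons between A&T-intensive and A&T-non intensive". It then adds that "double difference estimates will ensure greater statistical power". It attaches no condition, gives no between-round correlation and reports no power for the double difference.

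The section on sample size and power describes the data: "Surveys are repeated cross-sectional, surveying different households/children from the same communities". It sets the sizes per arm at "500 infants 0-5.9 months old for EBF, 500 children 6-23.9 months old for complementary feeding-related practices, and 1,100 children 24-47.9 months old for stunting", "in a total of 20 clusters with an inter-cluster correlation (ICC) of 0.005, a significance level of 0.05, and power of 80 percent". The Evaluation Design section assigns upazilas "to either the *intensive* (10 sub-districts) or *non-intensive* (10 sub-districts) intervention".

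The SAP, under its detailed statistical analysis approach, makes the double difference the impact estimate: "Impact estimates in Bangladesh will be double difference estimates of changes in key impact indicators". It is to be fitted with village fixed effects. The adjusted analysis names child age, child sex and other variables that may differ between arms. It does not name the upazila's baseline level of the outcome.

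**The concern.** When the same children are measured twice, differencing removes stable child-level variation and often improves precision. That does not carry over to independent cross-sections. Only the stable part of the upazila (or village) effect cancels, while the child-level sampling error of the baseline round is added to that of the endline round. Whether the result is a gain or a loss depends on how much of the variance of an upazila mean is true between-upazila variance, and on how stable that is over four years.

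The footnote serves as reassurance: a reader takes the tabulated differences as conservative because the planned estimator will do better. If between-round correlation is modest, the planned estimator does worse than the comparison on which the table rests. The same data would also support a baseline-adjusted analysis that avoids most of that loss, and the SAP does not list one.

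**Working it through.** **Inputs.** Ten upazilas per arm. Dividing the planned sizes per arm by 10 gives m = 110 children per upazila (stunting, HAZ) or 50 (EBF, minimum acceptable diet). No anemia size is stated, so m = 50 is assumed because the age group is the same. Upazila ICCs from Table 3: stunting 0.02, HAZ 0.05, EBF 0.12, minimum acceptable diet (MAD) 0.04, anemia 0.00. The design ICC is 0.005. The true between-round correlation of upazila levels, r, is not in the documents and is varied. Variances are taken as equal at both rounds.

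**The plan's own figure.** The stunting row reads "50.9 | 10 pp | 0.02 | 920". A one-sided 5% test at 80% power with continuity correction, 50.9% v 40.9%, gives n = 326 per arm before clustering. With k = 10 clusters per arm, N = k·n(1 − ICC)/(k − n·ICC) = 10 × 326 × 0.98/(10 − 6.52) = 918, or 920 when rounded up to whole children per upazila. This reproduces the table and confirms that it is an endline calculation with no baseline term. A two-sided test would give 1,717 without the correction. The EBF and MAD minimums do not reproduce from the printed baselines, but the variance ratios below do not use them.

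**Formulas.** The reliability of an upazila mean is λ = ICC/[ICC + (1 − ICC)/m]. The correlation of observed upazila means between rounds is R = r·λ. Variance relative to endline-only is:

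- double difference: 2(1 − R), below 1 only if R > 0.5, that is r > 0.5/λ;
- endline model adjusted for the upazila baseline value: 1 − R² in large samples.

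For stunting, λ = 0.02/(0.02 + 0.98/110) = 0.692 and the break-even is r = 0.5/0.692 = 0.72.

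| Outcome | λ (largest R) | Break-even r | Double difference at r = 0.5 / 0.7 / 0.8 | Baseline-adjusted at r = 0.5 / 0.7 / 0.8 |
|---|---|---|---|---|
| Stunting | 0.692 | 0.72 | 1.31 / 1.03 / 0.89 | 0.88 / 0.77 / 0.69 |
| MAD | 0.676 | 0.74 | 1.32 / 1.05 / 0.92 | 0.89 / 0.78 / 0.71 |
| HAZ | 0.853 | 0.59 | 1.15 / 0.81 / 0.64 | 0.82 / 0.64 / 0.53 |
| EBF | 0.872 | 0.57 | 1.13 / 0.78 / 0.60 | 0.81 / 0.63 / 0.51 |
| Anemia | 0 | none | 2.00 throughout | 1.00 throughout |

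**Design ICC of 0.005.** λ is 0.356 (m = 110) or 0.201 (m = 50). Even at r = 1 the double-difference variance is 2(1 − 0.356) = 1.29 or 2(1 − 0.201) = 1.60 times the endline-only variance.

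**In power terms.** Stunting, 10 pp, 1,100 per arm, with a two-sided 5% test on 18 df (17 with the covariate) assumed: endline-only 71%. Double difference v baseline-adjusted: 59% v 76% at r = 0.5, 70% v 82% at 0.7, 76% v 85% at 0.8. The adjusted figures use 1 − R² and omit the cost of estimating the slope, roughly 6% of variance with 20 upazilas.

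**Twenty upazilas.** In 40,000 simulated trials per value of R, power for adjustment v double difference was 87.5% v 79.8% at R = 0.5 and 79.9% v 79.8% at R = 0.872. At R = 0.90 it was 79.3% v 79.9%. With division terms added, the comparison was 86% v 78% at R = 0.5 and 79% v 78% at R = 0.8, and the advantage was gone by 0.85.

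**The case against.** The strongest reply is that the double difference may well gain. At r = 0.8 it is more precise than the endline comparison for four of the five rows, and at r = 0.7 it gains clearly for HAZ and EBF and is near parity for stunting and MAD. This stands. A reader might infer that the double difference usually loses power, but the documents do not support that. A loss is certain only for anemia and at the design ICC, and the latter was set before the baseline ICCs in Table 3 were available.

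Second, returning to the same villages can raise R. With an assumed extra village ICC of 0.02 to 0.10, the stunting break-even falls from 0.72 to 0.70–0.63. With a village ICC of 0.05 to 0.10, the design-ICC stunting case could also pass, at r above 0.93–0.77. Anemia still cannot reach R = 0.5 (largest R 0.36). This softens the thresholds and does not restore a guarantee.

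Third, a reader might infer that baseline adjustment always beats the double difference. That is a large-sample result. With 20 upazilas the advantage disappears at about R = 0.88–0.90, just above the highest cap in the table (0.872), or at about 0.85 with division terms.

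Fourth, a reader might infer that the trial is already underpowered and that the footnote hides it. Table 3's own stunting minimum (920) is below the planned 1,100. The 71% above depends on a two-sided test, which the documents do not state, and that is a separate question.

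Finally, the double difference is valid under randomization and matches main outcomes that the plan defines as changes. Keeping it as the headline is a defensible choice.

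**Conclusion.** The footnote's unconditional claim is wrong as written. A gain over the endline comparison requires R > 0.5, meaning a true four-year upazila correlation above about 0.72 (stunting), 0.74 (MAD), 0.59 (HAZ) or 0.57 (EBF), and the documents report none. For anemia the variance roughly doubles. If the printed 0.00 is a rounded value just under 0.005, the ratio is still at least about 1.60 at m = 50. Over r = 0.5 to 0.8, the variance relative to endline-only runs from 1.31 to 0.89 for stunting and from 1.13 to 0.60 for EBF, so the direction is unknown for these outcomes.

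This rests on Table 3's upazila ICCs, the planned sizes (50 per upazila assumed for anemia), equal variances at both rounds and no extra village-level correlation. The estimator is not invalid and the sample size was not derived from the footnote. What fails is the assurance. The SAP also omits an adjusted analysis that is at least as efficient in large samples.

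**What to change.** 1. Delete the guarantee in the Table 3 footnote, or replace it with double-difference detectable differences over a stated range of r, for example 0.5 to 0.9. Multiplying the tabulated endline difference by √[2(1 − R)] gives a first approximation. For stunting, 10 pp becomes 10 × √1.308 = 11.4 pp at r = 0.5 and 10 × √0.755 = 8.7 pp at r = 0.9. For EBF, 20 pp becomes 20 × √1.128 = 21.2 pp and 20 × √0.430 = 13.1 pp.

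2. Beside the double difference, pre-specify an endline child-level model on arm and the upazila-level baseline value of the same indicator, clustered on upazila. Use the upazila value and not the village value. With about 5 infants (50/10) or 11 older children (110/10) per village, a village covariate is so noisy that it can be less precise than the double difference: for EBF at r = 0.8, relative variance 0.65 against 0.60, assuming no extra village variance.

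The cost is SAP wording, one extra model on data already in the plan, and one degree of freedom for the covariate (20 − 3 = 17 left). Division terms would take four more (13 left). No new data are needed.

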**Sampling**

The sampling at endline will be identical to the sampling procedures followed at baseline and the same communities will be surveyed at both points in time:

- From each *upazila*, five unions will be randomly selected.
- Then, two villages will be selected randomly from each of the selected unions, to yield a total of 200 villages from which survey households will be selected. Only households with children 0-48 months of age were selected at baseline, and therefore, the same age group will be measured in the endline too.
- The baseline survey included a household listing during which a census of households in the 200 villages selected for the survey was conducted. This will now be repeated for the endline as well, following the same procedures as at baseline, including demarcations of villages into enumeration areas, if required.

## Data collection methods

The survey comprises of five main components:

- Household listing and census
- Household survey
- Anthropometric measurements of children and mothers and hemoglobin assessments
- Frontline worker surveys
- Community questionnaires

***Census form***: The census form will capture information captured at baseline, and will include administrative information of the location of the household, information on the household composition, and literacy and main occupation of all household members. The questionnaire will include, as at baseline, some basic household-level information as well as information on exposure to BRAC’s health program. In addition, the census questionnaire asked if the household had a child 0-48 months of age, to develop the on-site sampling list.

***Household questionnaire***

The household questionnaire will be administered to the mother of the index child chosen for the survey. In addition to the questionnaire-based data collection, anthropometric measurements (height and weight) will be taken for mother and index child in each household. The endline household questionnaire is being developed by using the baseline evaluation questionnaires as a base, and adapting it to capture key program activities, particularly with regards to the use of A&T community services and exposure to mass media. Table 4 below presents an overview of how the data collected in the household questionnaire is used in analysis and interpretation of impact results. We will explore the possibility of capturing exposure by fathers and grandmothers to the interventions but will need to explore this in light of the survey budgets.

**Table 4. Impact, process, and underlying factors captured by the baseline and endline household questionnaire**

| **Type of data** | **Questionnaire modules/questions** | **How used** |
| --- | --- | --- |
| Impact indicators | Child anthropometry  WHO-recommended IYCF indicators | Change between baseline and endline used to assess trends in impact indicators |
| Process data – client outcomes | Maternal IYCF knowledge  Awareness, trial, and adoption of key recommended practices  Behavioral determinants | Helps assess if IYCF knowledge shifted over project period, whether awareness of key recommended behaviors improved |
| Process data – client access, exposure, and utilization of services | Exposure to FLW counseling services and mass media  Utilization and coverage  Prenatal and postnatal care | Helps assess if exposure to intended program channels is as expected. Will also allow assessment of impact trends by levels of exposure to interventions |
| Influencing/underlying factors – child level | Child illness and health  Child development/milestones  Hygiene and hand washing | Helps assess if child-level factors modify influence of exposure to interventions. Child development milestones also function as an outcome/impact indicator in relation to IYCF practices and micronutrient powders. |
| Influencing/underlying factors –maternal level | Education, working condition, time constrains and child care arrangement.  Physical and mental well-being  Women’s status and maternal decision making power at the household | Maternal well-being is a prerequisite for intervention success. We would use these data to control for underlying mother factors and analyze the influence of mother constraints on ability to benefit from the A&T interventions. |
| Influencing/underlying factors – household level | Household SES (construction of SES scale from assets)  Household economic shocks  Household food security | Economic shocks could seriously undermine project impact. Additionally, improvements in SES over time could attribute greater impact to the project than is true. Therefore, data on SES, shocks, and food security are important both to control for these influences in analyses of change over time, as well as to examine the influence of household-level constraints on the ability to benefit from A&T interventions . |

***Frontline health worker questionnaire***

Gathering data on FLWs at baseline and endline enables us to document changes in FLW performance over time and contributes to an understanding of the impact pathways through which A&T objectives are met. Since FLWs are a critical factor in the overall impact and process pathways, it is essential to capture issues related to their performance as part of the overall evaluation. The literature on FLWs and their work context is slim in the field of nutrition programs and nutrition program evaluations. Based on the literature, available validated scales, and our past experiences studying this issue in evaluations, we have included in the A&T evaluation questionnaires the following domains (Table 5) that relate to frontline health workers and their performance, particularly in relation to IYCF counseling. If deemed necessary, we could also interview village doctors (who were interviewed at baseline).

**Table 5. Overview of the domains covered in the A&T frontline health worker questionnaires**

| **Domains** | **Rationale for inclusion** | **How used in evaluation** |
| --- | --- | --- |
| Technical knowledge and skills related to IYCF | A basic prerequisite for delivering the franchise model successfully is knowledge of FLWs about the core topics to be covered in the franchise model. We included the same IYCF knowledge assessments for FLWs and mothers in our questionnaires. Empirical evidence indicates that the amount of correct knowledge that is shared by FHWs and beneficiaries influences the probability that beneficiaries will try new behaviors. | Document improvements/shifts in technical knowledge and skills due to A&T inputs |
| Training exposure | In order to effectively deliver the IYCF service delivery package, FLWs require training to develop their competency in performing required duties. In addition, training is known to be a motivating influence on FHWs. | Document exposure of FLWs to training and impact of training |
| Media exposure | Mass media advertisements have potential to influence FHWs’ knowledge, work and behaviors. | Evaluate impact of mass media |
| Work load and time commitments | Information on workload and time commitments are needed for three purposes: 1) to understand demands made by A&T on workload and time commitments; 2) to understand how perceptions of workload, in addition to actual workload, influence FLW motivation and performance; and 3) to use data on time commitments, and shifts in time commitments and activities due to the interventions in the costing studies. | Compare baseline and endline. Used in costing component to estimate changes in time allocations due to A&T |
| Motivation and job satisfaction | A number of factors influence FLW motivation. These include factors that are extrinsic to the FHW as well as intrinsic motivators. Motivation is strongly related to job performance; therefore, capturing perceptions related to motivation and motivators is important both at the baseline and endline as well as in the interim (process evaluation). Job satisfaction is also an influence on job performance, and therefore important to capture. | Establish baseline; document shifts in motivation/job satisfaction due to A&T inputs such as training, incentives, supportive supervision. |
| Self-efficacy and confidence | Self-efficacy and confidence is a basic driver of job motivation and job performance. | Establish baseline; document improvements/shifts due to A&T inputs and assess role of confidence/self-efficacy in performance of FLWs |
| Supervisory support | Supportive supervision is documented to be critical in FLW performance, motivation, and training. | Establish baseline; document improvements/shifts due to A&T inputs and assess/document role of supervisory support in performance of FLWs implementing A&T interventions |
| Basic demographics | Demographic characteristics may have influences on worker performance and effectiveness. | Control for basic demographics in analyses of factors. |

